#### 2.2.2. Recruitment

A call for participation will be disseminated through the official channels of Club Tigres (website and social media) and by email to club subscribers, detailing the general characteristics of the program, participation criteria, expected benefits, and additional incentives. Likewise, academic research centers will support the promotion of the program through their communication channels.

An online registration form will be provided, requesting basic information that will serve as a preliminary eligibility assessment. In addition, contact options by phone and by email will be made available to provide information and to resolve any questions. Finally, a follow-up will be conducted with individuals who express their intention to participate in the program.

#### 2.2.3. Inclusion, Exclusion, and Withdrawal Criteria

The inclusion, exclusion, and elimination criteria for this study will be based on those established by the TIGREFIT program [39].

Inclusion Criteria. Men and women aged 35 to 50 years, with a body mass index (BMI) between 28 and 34.9 kg/m^2^, performing less than 150 min of moderate to vigorous physical activity per week, with at least a secondary education level, access to medical health services, and who provide consent to participate in the study and randomization.

Exclusion Criteria. Individuals with uncontrolled medical conditions, use of medications that significantly alter metabolism, diagnosis of severe psychiatric disorders, pregnancy or breastfeeding, recent or chronic musculoskeletal injuries that limit physical activity, participation in other weight loss or physical activity programs, excessive alcohol or psychoactive substance use, difficulties understanding the study language, or lack of time availability to follow the program.

Withdrawal Criteria. Participants who voluntarily withdraw from the program or those who fail to fully complete the evaluation instruments. 

The overall study procedure is presented in Figure 1.

#### 2.2.4. Sample Size and Randomization

The study will employ a non-probabilistic convenience sampling [44], including participants who meet the established inclusion criteria and are available during the recruitment period.

The sample size (*n* = 80) was determined pragmatically and based on operational feasibility, considering the resources and organizational requirements of the intervention, including the facilitators’ capacity, the availability of staff responsible for implementation, the total program duration, and the estimated recruitment period.

The participants will be distributed equally between the two intervention modalities, with 40 participants per modality (20 men and 20 women in each; see Table 1).

Randomization will be conducted using a computer-generated procedure, applying stratification to ensure an equitable distribution between the groups. The randomization will be generated and safeguarded by a researcher independent of the intervention. Once the assignment is generated, each participant will be notified individually.

Blinding of the participants and facilitators is not feasible due to the nature of the intervention delivery format. The face-to-face and semi face-to-face modalities differ in observable aspects, such as the type of interaction, communication channels, and module dynamics, making it impossible to conceal the assigned modality. Nevertheless, participants will not receive information regarding the activities or specific structure of the alternative modality. Likewise, facilitators will necessarily be aware of the format of the modality they deliver.

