## Abstract

**Background**: A sedentary behavior and being overweight represent major public health issues associated with both physical and psychological risks. Based on self-determination theory (SDT), the psychoeducational intervention PsicoFIT—a component of the TIGREFIT program—aims to foster motivation toward physical activity, to promote healthy habits, and to reduce psychological ill-being in sedentary adults who are overweight and are fans of a football club. **Methods**: This protocol corresponds to a longitudinal comparative pragmatic clinical trial, designed in accordance with the recommendations of the SPIRIT Statement. The intervention, preceded by a training program for the coaches involved, will comprise 12 weekly modules delivered in two modalities: (1) face-to-face, through group sessions, and (2) semi face-to-face, through short video capsules hosted on a digital platform. Changes associated with the intervention will be evaluated using hierarchical multiple regression and pre-post comparisons, assessing baseline and post-intervention data within and between the intervention modalities. Primary outcomes will include changes in healthy lifestyle and burnout as indicators of well-being and ill-being, respectively. Secondary outcomes will assess basic psychological needs satisfaction and autonomous motivation as potential mediators of these effects, as well as the coach’s controlling interpersonal style as a possible contextual predictor. The modality of participation will be analyzed as a potential moderator of the observed changes. Finally, the acceptability and perceived contribution of the intervention will be explored through a focus group. **Discussion**: PsicoFIT will provide a methodological framework for designing interventions within multicomponent programs aimed at promoting healthy lifestyles and psychological well-being in sedentary adults who are overweight, considering the social context of football fandom and allowing for an exploration of the impact of the face-to-face and semi-face-to-face modalities. Future empirical application of the protocol will help verify its effectiveness, guide adaptations across contexts, and contribute to the development of evidence-based interventions. **Conclusions**: The implementation of PsicoFit will allow for the evaluation of its effectiveness, psychological mechanisms, and delivery modalities, thus guiding future evidence-based interventions in sport.

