### 2.3. Data Collection

#### 2.3.1. Quantitative Evaluation

Quantitative evaluation was conducted using validated and reliable self-report instruments, administered at baseline (time 1) and at the end of the intervention (time 2). Although such measures may be subject to response biases, including social desirability or recall errors, the use of questionnaires with adequate psychometric properties allows for a representative assessment of the variables in the context of the intervention.

Controlling Style of the Coach. The Mexican version of the Controlling Coach Behaviors Scale (CCBS) [51], adapted from the Spanish version [52], will be used. It consists of 15 items on a 7-point Likert scale from 1 (*strongly disagree*) to 7 (*strongly agree*), measuring four controlling motivational strategies in sport: negative conditional regard, intimidation, controlling use of rewards, and excessive personal control. This scale has shown adequate reliability and validity [51,52,53], and has been previously used in exercise and well-being promotion contexts [54].

Psychological Needs Satisfaction. The following instruments, adapted and validated in the Mexican context [55], will be used:Perceived Autonomy in Sport Scale (PASS) [56], Spanish version [57], which consists of 10 items on a 7-point Likert scale from 1 (*not at all true*) to 7 (*very true*), evaluating two facets of perceived autonomy: decision-making and volition. The scale has demonstrated adequate reliability and validity [55,56,57].Perceived Competence Scale from the Spanish version [57] of the Intrinsic Motivation Inventory (IMI) [58], which is composed of 5 items on a 7-point Likert scale from 1 (*strongly disagree*) to 7 (*strongly agree*), measuring perceived competence in sport. The scale has demonstrated adequate reliability [57,58].Need for Relatedness Scale [59], Spanish version [57], which consists of 5 items on a Likert scale from 1 (*strongly disagree*) to 5 (*strongly agree*), measuring perceived acceptance and respect in the sport context. The scale has demonstrated adequate reliability and validity [55,57,59].Although these instruments originate from the sports domain, their applicability extends to exercise and well-being contexts, and are recognized by SDT as suitable environments for fostering basic psychological needs [20,21].

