#### 2.3.3. Assessment Timeline

Evaluations will be conducted at the following times:Time 1. Week 0: What is My Lifestyle Like? Survey.Time 1. Week 2: Controlling Coach Behaviors Scale, Perceived Autonomy in Sport Scale, Perceived Competence Scale, Need for Relatedness Scale, Sport Motivation Scale II, and Athlete Burnout Questionnaire. The questionnaires will be administered at this point because they will assess the variables that require the participants to have previously interacted with the program components in order to be appropriately perceived.Time 2. Week 13: All instruments and the focus group will be administered.

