#### 2.3.4. Data Management

The instruments will be administered in a computer lab using the QuestionPro platform. The collected information will be exported to an Excel database, coded, and prepared for analysis in statistical software.

To safeguard the data, periodic backups will be performed on a secure institutional cloud storage service and a portable external storage device maintained by the research team.

To ensure data quality and accuracy, two researchers will independently enter the information, after which both versions will be compared to detect possible discrepancies or coding errors.

**Table 1 healthcare-14-00612-t001:** SPIRIT Schedule for Enrollment, Interventions, and Assessments.

Study Period																
	Enrollment	Allocation		Intervention												Post-Intervention
Time point			w0	w1	w2	w3	w4	w5	w6	w7	w8	w9	w10	w11	w12	w13
Recruitment	X															
Eligibility screening	X															
Informed consent	X															
Allocation		X														
Registration		X														
Interventions																
Intervention A: 12 weeks of face-to-face PsicoFIT with group 1				X	X	X	X	X	X	X	X	X	X	X	X	
Intervention B: 12 weeks of semi face-to-face PsicoFIT with group 2				X	X	X	X	X	X	X	X	X	X	X	X	
Assessments																
Controlling style of the coach					X											X
Psychological needs satisfaction					X											X
Autonomous motivation					X											X
Healthy lifestyle			X													X
Burnout					X											X
Focus group interview																X

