#### 2.7.1. Primary Outcomes

Healthy lifestyle (well-being): Behaviors related to nutrition, physical activity, and other healthy habits will be assessed as indicators of well-being.Burnout (ill-being): Physical and emotional exhaustion, sense of accomplishment, and devaluation of sports practice will be evaluated as indicators of ill-being.The variable of interest in both cases will be the change after the intervention, calculated as the difference between post-intervention and baseline scores.

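### As scheduled, the self-reported lifestyle baseline, one of two primary outcomes, is likely answered after participants learn their modality

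*Protocol article*

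**What the plan says.** All references are to the Protocol article.

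- **Notification and blinding (section 2.2.4).** "Once the assignment is generated, each participant will be notified individually". The same section says "Blinding of the participants and facilitators is not feasible due to the nature of the intervention delivery format". It adds one partial safeguard: participants are not told what the other modality involves.
- **Timing of the baseline (section 2.3.3).** "Time 1. Week 0: What is My Lifestyle Like? Survey". The other questionnaires have their first administration at week 2, because they need prior contact with the programme. That reason is not given for the lifestyle survey.
- **Schedule (Table 1, "SPIRIT Schedule for Enrollment, Interventions, and Assessments").** Allocation is marked in its own column. The next column is w0, which holds the first healthy-lifestyle mark. The intervention starts at w1.
- **Role of the outcome (Abstract and section 2.7.1).** "Primary outcomes will include changes in healthy lifestyle and burnout as indicators of well-being and ill-being, respectively". The variable of interest is the change, "calculated as the difference between post-intervention and baseline scores".
- **Analysis (section 2.6.1).** Change is examined within each modality and compared between modalities.
- **Response bias (section 2.3.1).** It is acknowledged only in general terms: "Although such measures may be subject to response biases, including social desirability or recall errors". Knowledge of allocation at baseline is not mentioned.

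**The concern.** A baseline is protected by randomisation when it is fixed before the participant knows the arm. Read together, the notification sentence and Table 1 suggest that this is not so here.

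The lifestyle survey has 45 agree/disagree items, some of them on physical activity, nutrition, rest and sense of life. Someone who has just learned the modality may answer differently out of anticipation or disappointment. The two modalities are not alike: section 2.4.2 gives one arm two two-hour football-based sessions a week and the other two video sessions averaging 24 minutes. A preference among recruited football supporters is plausible.

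Because the endpoint is a difference from baseline, an arm-related shift in baseline is counted as an effect of modality in the opposite direction. A shift common to both arms cancels between arms but remains in the within-arm pre-post comparisons.

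**Working it through.** **1. Order of events.** The plan states no figure on this point, so there is none to reproduce. The order has to be read from the schedule.

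| Event | Place | Position |
|---|---|---|
| Allocation | Table 1 | column directly before w0 |
| Notification | Section 2.2.4 | once the assignment is generated; no week given |
| First lifestyle survey | Section 2.3.3 and Table 1 | w0 |
| First module | Table 1 | w1 |

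Allocation precedes the survey in Table 1. Notification is tied to generation of the assignment, so it also precedes the survey unless it is held back. Nothing in the text holds it back or places the survey first.

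**2. How a shift carries through.** Suppose knowledge of allocation moves the baseline mean in one arm by s (in SD units), with no effect on the week-13 answer. The between-arm difference in change is then biased by −s. In a model adjusted for baseline with slope r, the bias is −r·s, which is smaller but not zero.

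**3. Illustration of size.** The plan gives no SD, correlation or shift, and sets n = 80 on feasibility. The inputs are:

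- from the plan: 40 per arm (section 2.2.4) and 5% error (section 2.6.1);
- assumed: a two-sided test, all 40 per arm completing, no true difference, baseline–post correlation r, and shift s.

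Formulas (normal approximation, outcome SD = 1):

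- SD of change = √(2(1 − r))
- SE of the contrast = SD of change × √(2/n)
- λ = s / SE
- rejection rate = Φ(λ − 1.96) + Φ(−λ − 1.96)

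For r = 0.5, the SD of change is √(2 × 0.5) = 1 and the SE is √(2/40) = 0.224. With s = 0.1, λ = 0.1/0.224 = 0.447 and the rate is Φ(−1.513) + Φ(−2.407) = 7.3%. With s = 0.2, λ = 0.894 and the rate is Φ(−1.066) + Φ(−2.854) = 14.5%.

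| Shift s | Change score, r = 0.5 | Change score, r = 0.7 | Baseline-adjusted, r = 0.5 |
|---|---|---|---|
| 0 | 5.0% | 5.0% | 5.0% |
| 0.1 SD | 7.3% | 8.9% | 5.8% |
| 0.2 SD | 14.5% | 21.1% | 8.1% |
| 0.3 SD | 26.9% | 41.0% | 12.1% |

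The adjusted column uses bias r·s and SE = √(1 − r²) × √(2/n). With 30 completers per arm and r = 0.5, the change-score rates at 0.1 and 0.2 SD are 6.7% and 12.1%.

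**4. After the fix.** If the survey is finished before disclosure, s = 0 by design and the rate returns to 5% as far as this bias is concerned. The sample size does not change.

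**The case against.** **The order is inferred.** No sentence dates notification relative to week 0, Table 1 has no row for notification, and the flow diagram (Figure 1) is not available in the text reviewed. The header cell above w0 is blank there, so w0 may belong to the allocation period. This stands as a limit on certainty: a reader might infer that the baseline is definitely collected after disclosure, and the document does not go that far. It does not reverse the order, because the allocation mark itself sits before w0.

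**Safeguards exist.** Participants are not told the content of the other modality, they consent to randomisation as an inclusion criterion (section 2.2.3), and both arms receive an active programme. Several of the ten lifestyle factors, such as oral health, have no obvious link to delivery format. These points lessen the risk. They do not remove it, since each person knows their own modality and other factors are more exposed.

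**Early leavers are a separate matter.** A reader might infer that people who leave on learning their allocation are lost because the baseline comes late. Sections 2.5.9 and 2.6.1 do not support that. Only participants with both assessments are analysed, without imputation, so such a person is excluded wherever the baseline falls. Section 2.6.1 already concedes that the benefits of randomisation may not be fully preserved.

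**The size is hypothetical.** This also stands. In particular, 0.63 SD should not be read as this trial's detectable difference. The plan gives no power calculation, and for a change score that value holds only at r = 0.5 with 40 completers per arm, two-sided 5% and 80% power (about 0.49 SD at r = 0.7).

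**Conclusion.** The concern holds as a risk created by the schedule as written. Allocation precedes w0 in Table 1 and unblinded participants are told once the assignment exists, so the lifestyle baseline is likely answered with knowledge of the modality. Any arm-related shift enters the primary change contrast in full, with opposite sign.

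The documents give neither its size nor its direction. Under the assumed values (40 completers per arm, r = 0.5, no true difference, a shift confined to one arm's baseline), 0.1 to 0.2 SD would raise the false-positive rate from 5% to about 7% to 15%. A shift that persisted unchanged to week 13 would cancel in the change score. The figures therefore describe sensitivity and do not predict what will happen in this trial.

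The bias is avoidable at little cost, so the sequence should be corrected. The point concerns the lifestyle outcome only; burnout is first measured at week 2, which is a separate question.

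**What to change.** State the sequence in sections 2.2.4 and 2.3.3, for example: *Participants complete the lifestyle survey after giving consent. The allocation is generated, and disclosed to the participant, only after the survey has been submitted.* If generation cannot wait, disclosure at least should. Reorder Table 1 so that the w0 lifestyle assessment comes before allocation, and add a row for notification. If notification already follows the survey in practice, only the text and table need correcting.

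The instrument and the sample size stay the same, and the survey needs no exposure to the programme. The cost is scheduling: section 2.3.4 has the instruments completed in a computer lab, so a lab slot is needed between consent and disclosure. The document does not show whether this fits an existing visit.

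Adjusting for baseline would not replace this change, since it reduces the bias to r·s without removing it. Nor would the change cure the loss of participants who leave on learning their allocation. It would provide a baseline score by which those early leavers could be described by arm.

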#### 2.2.5. Participant Retention

Strategies to promote retention in the study will include informational and engagement approaches. An induction session will be conducted to explain the details of the intervention and the schedule of activities, with the aim of reminding the participants of the expected benefits, the importance of their participation, and helping them organize their availability for the program.

Additionally, social incentives linked to Club Tigres will be offered, such as visits to training sessions, match tickets, or interactions with club players.

Participants who accumulate consecutive absences or fail to report viewing the video capsules, whichever the case, will be offered support to continue.

In the case of voluntary withdrawal, the participants will be given the possibility to rejoin the study if feasible; otherwise, they will be considered for future editions of the program.

If a participant leaves the study, their contact information and completed evaluations will be recorded. When possible, they will be asked to complete a survey regarding their experience and reasons for leaving.

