### 2.6. Data Analysis

#### 2.6.1. Quantitative Analysis

Due to the practical limitations in following up with those participants who do not complete the program, the primary analysis will be conducted using a per-protocol approach [111], considering only those participants with complete data at baseline and at the end of the intervention; missing data will not be imputed.

This approach will allow for evaluating the changes associated with each intervention under real-world implementation conditions, acknowledging the anticipated risk of participant attrition and that the benefits of randomization may not be fully preserved, while reflecting its applicability in a pragmatic context.

All statistical analyses will consider a 95% confidence level (5% error), ensuring transparency and reproducibility.

Preliminary Analysis. Descriptive statistics for central tendency (mean, median), dispersion (standard deviation and variance), and distribution (skewness and kurtosis) will be estimated for each observed variable. Next, normality tests will be conducted, and the reliability of the instruments will be estimated by measuring their internal consistency through Cronbach’s alpha (α) and McDonald’s omega (ω) coefficients. Subsequently, bivariate correlation analyses will be performed to measure the strength and direction of the relationship between the variables.

Associations among motivational and outcome variables. To examine the associations between the coach’s controlling interpersonal style, basic psychological need satisfaction, autonomous motivation, healthy lifestyle, and burnout, hierarchical multiple regression analyses will be conducted. Separate models will be estimated for each intervention modality (face-to-face and semi face-to-face) and for each measurement occasion (baseline and post-intervention), with predictor variables entered in a theoretically driven manner [42]. Effect sizes and confidence intervals will be calculated to complement the statistical significance, and statistical power will be considered when interpreting the results [112].

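### The leaving procedure provides only for an exit survey, with no stated request for the week-13 outcome questionnaires, so formal withdrawers are likely to have no observed outcome

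*Protocol article*

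**What the plan says.** - **Who counts as withdrawn.** Section 2.2.3 defines this as "Participants who voluntarily withdraw from the program or those who fail to fully complete the evaluation instruments". Stopping the programme is not separated from leaving the assessments.
- **What is kept and requested.** Section 2.2.5 states: "If a participant leaves the study, their contact information and completed evaluations will be recorded". The one new request is: "When possible, they will be asked to complete a survey regarding their experience and reasons for leaving". For those who withdraw by choice, the same section says: "the participants will be given the possibility to rejoin the study if feasible; otherwise, they will be considered for future editions of the program". Outcome assessment of someone who does not rejoin is not mentioned.
- **When and how outcomes are measured.** Section 2.3.3 schedules all instruments at week 13. The lifestyle survey has its baseline at week 0; the Athlete Burnout Questionnaire (ABQ) has its baseline at week 2. Section 2.3.4 adds: "The instruments will be administered in a computer lab using the QuestionPro platform".
- **What is analysed.** Both primary outcomes are post-intervention minus baseline scores (section 2.7.1). Section 2.6.1 justifies its per-protocol primary analysis as follows: "Due to the practical limitations in following up with those participants who do not complete the program". The analysis is described as "considering only those participants with complete data at baseline and at the end of the intervention; missing data will not be imputed". Section 2.5.9 likewise limits the dataset to people with both assessments.

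**The concern.** This is a point about what is collected, and it comes before the choice of analysis set. Widening the analysis set later would not supply a week-13 score that nobody requested. With only one post-baseline occasion, a withdrawer without that score contributes no observed outcome to any model.

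Participants are randomised so that the two modalities can be compared (section 2.1), and attrition is expected (section 2.6.1 and the Discussion). Unequal leaving is plausible because the weekly load differs so much. From sections 2.4.2, 2.4.3 and 2.5, face-to-face comes to 60 + 240 + 40 + 30 + 30 = 400 minutes, before nutritional counselling. Semi face-to-face comes to 60 + 48 + 40 + 5 + 5 = 158 minutes, taking the nutrition capsules as weekly. Motivation and burnout may themselves drive leaving. If leavers improve less, each within-modality change looks better than it was. If more of them leave one modality, the comparison is tilted towards that modality.

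**Working it through.** **No figure to reproduce.** The sample of 80 (40 per modality) is a feasibility figure (section 2.2.4). The protocol gives no effect size, SD or attrition rate. Everything below except the 40 per modality is an assumption, used only to show scale.

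**Step 1: the sections side by side.** Section 2.2.3 makes leaving the programme a withdrawal. Section 2.2.5 plans an exit survey and retains existing data. Section 2.3.3 schedules week 13 without mentioning leavers. Section 2.6.1 gives limited follow-up of non-completers as the reason for complete cases only. Followed as written, these leave formal withdrawers without a week-13 score unless they rejoin.

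**Step 2: bias among completers.** Let *p* be the share leaving a modality and *d* the amount, in SD of change, by which leavers improve less than stayers. The mean for all randomised participants is the stayers' mean minus *p·d*, so completers overstate the change by *p·d*. The between-modality bias is *d*(*p*₁ − *p*₂).

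**Step 3: bias if half the leavers, taken at random, return scores.** The observed mean is then the stayers' mean minus *d*(*p*/2)/(1 − *p*/2), so the bias is *p·d* − *d*(*p*/2)/(1 − *p*/2).

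- For *p* = 0.35: *d* × (0.35 − 0.175/0.825) = 0.138*d*
- For *p* = 0.25: *d* × (0.25 − 0.125/0.875) = 0.107*d*
- For *p* = 0.15: *d* × (0.15 − 0.075/0.925) = 0.069*d*

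| Leaving | *d* (SD) | Between-modality bias, completers only | With half retrieved at random |
|---|---|---|---|
| 25% v 15% | 0.5 | 0.125 − 0.075 = 0.05 | 0.054 − 0.034 = 0.02 |
| 35% v 15% | 0.5 | 0.175 − 0.075 = 0.10 | 0.069 − 0.034 = 0.03 |
| 35% v 15% | 0.8 | 0.280 − 0.120 = 0.16 | 0.110 − 0.055 = 0.06 |

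In the modality losing 35%, the within-modality overstatement falls from 0.18–0.28 SD to 0.07–0.11 SD.

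**Step 4: precision at 35% v 15%.** Completers number 26 + 34 = 60, so SE = √(1/26 + 1/34) = 0.26 SD. With half the leavers retrieved, 33 + 37 = 70 and SE = √(1/33 + 1/37) = 0.24 SD.

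**Step 5: the unfavourable limit.** If the leavers who respond have the same mean as stayers, the observed mean stays at the stayers' mean and the bias stays at *p·d*. Random retrieval is therefore the favourable case.

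**The case against.** A reader might infer that the protocol rules out collecting outcomes from leavers, that everyone who attends poorly is lost, and that nothing afterwards can be done for these participants. The protocol does not support any of these.

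- **No prohibition.** No sentence forbids asking leavers, and section 2.3.3 restricts week 13 to no subgroup. The parent programme's criteria, the flow figure and the supplementary checklist are not visible. What stands is that the leaving procedure is written out without such a request, and section 2.6.1 reads as though these outcomes will not be available.
- **A narrower group.** There is no attendance threshold. People with repeated absences or unviewed capsules are offered support and can still be assessed, and voluntary leavers may rejoin. The gap concerns formal withdrawers.
- **No contradiction over follow-up.** The exit survey is conditional on being possible, which is compatible with practical limits on follow-up. It does show that some contact is envisaged.
- **Analysis is not wholly powerless.** Baseline data are kept, so imputation from baseline could be run under untestable assumptions. Section 2.6.1 excludes imputation, and no method recovers the actual week-13 values.
- **Burnout is harder.** Anyone leaving before week 2 has no ABQ baseline and so no change score. Scores from people who stopped the activity weeks earlier are also hard to interpret. The argument is clean only for the lifestyle survey.
- **Disclosure.** Section 2.6.1 and the Discussion admit attrition and possible bias. That is candid, but it neither removes the bias nor adds any data.
- **Size.** The mildest scenario moves the bias only from 0.05 to 0.02 SD, against a standard error near 0.25 SD.

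**Conclusion.** The point holds as a gap in planned data collection that should be closed. Formal withdrawal from the programme is treated as withdrawal from the study, no request for week-13 outcomes from these people is stated, and the resulting lack of follow-up is used to justify a complete-case primary analysis. If leaving is related to outcome, the within-modality changes are biased; if it also differs by modality, so is the randomised comparison. The protocol does not allow the amount to be estimated. The illustrative 0.05 to 0.16 SD between modalities depends entirely on assumed attrition of 25–35% v 15% and a leaver deficit of 0.5–0.8 SD. Collecting the outcomes would reduce this bias without eliminating it.

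**What to change.** 1. In sections 2.2.3 and 2.2.5, separate stopping the programme from withdrawing consent for data collection.
2. At week 13, invite every randomised participant who has not withdrawn consent to complete the lifestyle survey (45 items, week-0 baseline). Invite those with a week-2 baseline to complete the ABQ (15 items) as well. Offer a QuestionPro link to anyone who cannot attend the computer lab.
3. Send these in addition to the exit survey, so that reasons for leaving are not lost.
4. Record the mode of completion.
5. In sections 2.5.9 and 2.6.1, state that these scores enter the between-modality comparison by randomised group, and that a missing burnout score does not remove a usable lifestyle score.

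**Cost.** The change needs protocol and consent wording, ethics review, a link on a platform already in use, and reminders to people whose contact details are kept. Up to 60 items, some on sexuality and substance use, ask more of a leaver than an exit survey does.

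**Limits.** Some leavers will not respond, and those who do may resemble completers. Remote completion will largely coincide with having left, so mode and leaver status cannot be cleanly separated. Burnout scores from people who have stopped the activity need cautious interpretation.
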